#### Behavioural avoidance task

The primary outcome is the behavioural avoidance task (BAT) at 6 months postrandomisation. The BAT is a widely used measure of treatment outcomes for phobias in children.^6 21^ The BATs for the Alleviating Specific Phobias Experienced by Children Trial (ASPECT) trial are standardised for each stimulus and have been found to have good test–retest reliability^20 29^ and strong correlation with other outcome measures of anxiety and phobia.^30 31^ During a BAT, the child gradually confronts their phobic stimulus over 10 predefined steps of increasing difficulty; the child does not have to complete all the steps. For example, a child with spider phobia may start the BAT at step 0, standing outside of a room that has a spider contained in a box. Subsequent steps the child may take are: opening the door (step 1), passing through the doorway (step 2), through to holding the spider for 20 s (step 10). The number of steps the participant takes is the main unit of measurement recorded for analysis. The BAT also includes a measure of subjective units of distress whereby the child reports their level of fear at the start of the BAT, and at the last step completed (ranging from 0=no fear at all to 8=extreme fear).

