### Statistical analysis

#### Sample size

The proposed sample size and non-inferiority margin are based on two separate Cochrane reviews looking at the effects of psychotherapy for those experiencing anxiety. First, Wolitzky-Taylor *et al*
47 conducted a review on studies that used both observer-rated BAT-like assessments and self-report questionnaires on adults with specific phobias and reported an overall, large effect size of d=0.81. However, as the treatment may have a different effect on children, we also examined the review of Reynolds *et al*.^48^ This review was conducted on studies of children with specific phobias but used self-report questionnaires rather than observer-rated BATs. The review reported a large effect size (d=0.85) for multisession CBT. Prior meta-analyses suggest that a standardised mean difference of around 0.8 on the BAT scale is clinically important. Therefore, we set the non-inferiority margin to be half of this at 0.4.^49^ Assuming a correlation of 0.5 between baseline and final BAT measure, we would require 200 participants (100 in each arm) to have 90% power with a 2.5% one-sided significance level to demonstrate non-inferiority of OST compared with CBT. The therapy is delivered by therapists who will see approximately 15 patients each and we anticipate a weak therapist effect (intraclass correlation coefficient=0.01). This clustering will lead to a design effect of 1.14 which increases the number required per arm to 114. We further assume a 20% drop-out rate suggesting that total number of 286 children and young people (143 per arm) will need to be recruited to the study to demonstrate non-inferiority of OST compared with CBT.

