#### Data analysis

As this trial follows a randomised, parallel group, non-inferiority design, data will be analysed and reported according to both Consolidated Standards Of Reporting Trials (CONSORT) guidelines^50^ and the non-inferiority trials CONSORT extension.^51^ Baseline data, including demographic characteristics (eg, age, gender) and clinical measures (eg, BAT, RCADS), will be reported between the two randomised groups. Jones *et al*
49 recommend both per-protocol and intention-to-treat (ITT) analyses for non-inferiority designs. For an equivalence or non-inferiority trial, as opposed to a comparative trial, ITT analyses are not considered conservative, as any blurring of the difference between the treatment groups increases the chance of declaring equivalence. We follow this recommendation with the refinement that the main analysis of the primary outcome will be per protocol (or completers only) with a sensitivity analysis on the ITT population.^49^ We will require both the per-protocol and ITT analyses to demonstrate conclusive evidence to declare that OST is ‘non-inferior’ to multisession CBT. If the results of the analysis are discrepant (eg, the ITT rejects the null of inferiority but the per-protocol analysis does not or vice versa) then we will report the conflicting results from both analyses highlighting the inconclusive nature of the results. For the sake of the analysis, a participant in the OST group is defined as per protocol if they attend both the initial functional assessment and the rapid exposure therapy session. A participant in the CBT group is defined as per protocol if they attend at least four CBT sessions.

The primary outcome (mean BAT score at 6 months) and the secondary outcomes (ADIS, CAIS, EQ-5D-Y, CHU-9D, RCADS and goal-based outcome scores) will be compared between groups using mixed-effects linear regression with exchangeable correlation to allow for the clustering of outcomes within therapist. The analysis will be conducted controlling for baseline BAT score, site and stratifying variables (age group and baseline phobia severity). The null hypothesis of inferiority will be rejected if the two-sided 95% CI for the difference is wholly below 0.4 (the range of clinical non-inferiority).

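### The 0.4 margin is defined in SD units, but the decision rule applies it to a model difference in BAT steps without naming a standardising SD

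*Protocol article*

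**What the plan says.** Three sections of the protocol article bear on the primary decision rule.

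- **Sample size.** The margin starts from a standardised effect: "Prior meta-analyses suggest that a standardised mean difference of around 0.8 on the BAT scale is clinically important". The next sentence reads: "Therefore, we set the non-inferiority margin to be half of this at 0.4". So 0.4 is a number of standard deviations.
- **Behavioural avoidance task.** The BAT has 10 predefined steps starting from step 0, and "The number of steps the participant takes is the main unit of measurement recorded for analysis".
- **Data analysis.** The primary outcome is the mean BAT score at 6 months. It is compared by mixed-effects linear regression, adjusted for baseline BAT, site and the stratification factors. The rule is: "The null hypothesis of inferiority will be rejected if the two-sided 95% CI for the difference is wholly below 0.4". A parenthesis identifies 0.4 as the clinical non-inferiority range but gives no unit.

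The article does not say that the outcome or the estimated difference will be standardised, which SD would be used, what 0.4 SD is in steps, or which arm is subtracted from which. Non-inferiority must be shown in both the per-protocol and ITT analyses, so both depend on this threshold.

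**The concern.** The treatment coefficient from a linear model of a step count is itself in steps. Comparing its CI with 0.4 therefore sets a step difference against a margin that was defined in SDs. An analyst who follows the text as written would test a margin of 0.4 of one step, which is not the margin the trial was sized for unless the SD is 1 step.

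An analyst who recognises the intent still has to choose an SD. The unadjusted SD and the model's residual SD give different margins. In a non-inferiority trial the threshold should be settled before anyone sees the comparison.

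The sign also matters. More steps is the better result, so an upper limit on the CI guards against inferiority of OST only if the difference is CBT minus OST.

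**Working it through.** **Inputs (Sample size section).** Margin 0.4; "Assuming a correlation of 0.5 between baseline and final BAT measure"; the design is "to have 90% power with a 2.5% one-sided significance level to demonstrate non-inferiority of OST compared with CBT"; about 15 patients per therapist, ICC 0.01, drop-out 20%. The true difference is taken as 0.

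**1. Reproduce the plan's sample size, reading 0.4 as SD units.**

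- Without baseline adjustment: n per arm = 2 × (1.96 + 1.2816)² / 0.4² = 131.3.
- With baseline adjustment: × (1 − 0.5²) = × 0.75 = 98.5. The plan states 100.
- Design effect: 1 + (15 − 1) × 0.01 = 1.14; 100 × 1.14 = 114.
- Drop-out: 114 / 0.8 = 142.5, rounded to 143 per arm, 286 in total.

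This agrees with the plan. The SD is set to 1 and the factor 0.75 enters separately as the gain from baseline adjustment, so 0.4 is a fraction of the unadjusted SD.

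**2. Power as planned.** At an effective 100 per arm, the standard error in unadjusted SD units is √(2 × 0.75 / 100) = 0.1225. Power = Φ(0.4 / 0.1225 − 1.96) = 90.4%.

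**3. Power if 0.4 is compared with a difference in steps.** Power = Φ((0.4 / SD) / 0.1225 − 1.96), and the 95% CI half-width in steps is 1.96 × 0.1225 × SD. The article gives no BAT SD, so the SDs below are assumptions.

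| Assumed SD (steps) | Planned margin, 0.4 SD (steps) | 0.4 step in SD units | CI half-width (steps) | Power |
|---|---|---|---|---|
| 1 | 0.4 | 0.400 | 0.24 | 90% |
| 2 | 0.8 | 0.200 | 0.48 | 37% |
| 2.5 | 1.0 | 0.160 | 0.60 | 26% |
| 3 | 1.2 | 0.133 | 0.72 | 19% |
| 3.5 | 1.4 | 0.114 | 0.84 | 15% |

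The half-width passes 0.4 when the SD exceeds 0.4 / (1.96 × 0.1225) = about 1.67 steps. Beyond that, even an observed difference of exactly zero would fail the literal rule.

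**4. Direction of the error.** For any SD above 1 step, 0.4 step is less than 0.4 SD. The literal test is then stricter than planned and does not inflate the type I error. Below 1 step it would be too lenient.

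**5. Standardising by the residual SD.** The residual SD is √0.75 = 0.866 of the unadjusted SD. A margin of 0.4 residual SD is 0.4 × 0.866 = 0.346 unadjusted SD. Power = Φ(0.346 / 0.1225 − 1.96) = about 81%.

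**The case against.** The strongest reply is that the article never states a margin of 0.4 steps. The Data analysis section does not print a unit beside 0.4, and its parenthesis points back to the only margin the article defines, which is standardised. Read with the Sample size section, the difference is most naturally a standardised one, and the design is coherent on that reading. This stands as an account of what was probably meant. A reader might infer that the plan deliberately tests a 0.4-step margin, or that the sample size is wrong. The text supports neither.

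A second reply is that the choice of SD is ordinary SAP detail, and a SAP may exist that settles it. That is fair for the choice of standardiser, and it cannot be said that the SD will in fact be picked after the data are seen. It does not dispose of the point, because the article does more than leave a detail out. It states the decision rule, and as stated the rule does not match the margin defined one section earlier. A SAP that supplies the conversion would still leave this sentence to be corrected.

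Third, the size of the effect rests on SDs that the article does not give, and on an analyst taking the rule literally. Both are true. The power figures are conditional on both, and the residual-SD alternative costs only about 9 percentage points.

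**Conclusion.** The point holds as a mismatch between the defined margin and the written decision rule. The margin is 0.4 unadjusted SD. The rule applies 0.4 to a difference that the described model estimates in steps, and the two agree only at an SD of exactly 1 step.

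Taken literally, with assumed SDs of 2 to 3.5 steps and a true difference of zero, power is about 37% to 15% against the stated 90%. If a standardised difference is meant, the unspecified SD leaves power between about 90% (unadjusted) and 81% (residual).

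A reader might infer that the rule risks a false claim of non-inferiority, or that it is certainly far too strict. The article does not support either. With an SD above 1 step the literal rule errs on the conservative side, and how strict it is depends on an SD that is not reported. The point still matters because this one threshold decides the primary conclusion in both analysis sets.

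**What to change.** Rewrite the rule in the Data analysis section so that it fixes four things:

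1. **Unit.** The margin is 0.4 of the unadjusted SD of the 6-month BAT, as in the sample size calculation.
2. **Scale of the test.** Before unblinding, convert 0.4 SD to BAT steps with the blinded pooled unadjusted SD of the 6-month BAT, and compare the adjusted difference in steps and its 95% CI with that number. Alternatively, pre-specify that the adjusted difference and its CI are divided by that same SD.
3. **One value.** Use the same fixed SD for the per-protocol and ITT analyses, so that both face the same margin.
4. **Direction.** Define the difference as mean CBT minus mean OST, so that a CI wholly below the margin means OST is not unacceptably worse.

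Converting the margin to a number of steps is slightly cleaner, because the threshold is then a constant and the CI needs no allowance for estimating the SD. An SD computed without regard to arm also contains any between-arm difference, but the effect is small: at a true difference of 0.4 SD with equal arms it is √(1 + 0.4²/4) = 1.02 times the within-arm SD. The Blinding section keeps the statisticians blind to allocation while the trial is ongoing, so the SD can be obtained blinded.

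The cost is a few sentences. No new data are needed and the sample size stays at 286.

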### Economic evaluation

We are conducting an economic evaluation from the UK personal and social services perspective. This will take the form of a within-trial cost–utility analysis to determine the incremental cost per unit of quality-adjusted life years (QALYs) of OST compared with CBT in children with specific phobias. Costs will be calculated based on: (1) resources required to deliver the intervention and (2) individual-level use of health and social services by children and absenteeism from school for children or from work because of childcare for parents over the study period. Resource use will be multiplied by unit costs to arrive at total cost in each arm. QALYs will be calculated by measuring health-related quality of life using the self-reported EQ-5D-Y over the study period.

The resources required to deliver the OST intervention will be calculated using bottom–up estimation of the time spent by professionals as well as other resources used (including phobic stimulus acquisition, ie, animal hire). Individual-level service use data will be based on self-reported use of primary and secondary healthcare as well as social care using a standardised Resource Utilisation Questionnaire. Unit costs of health and social service use will be obtained from the UK national database of reference costs department of health,^52^ and the Unit Costs of Health and Social Care report produced by the Personal Social Services Research Unit.^53^ The cost of medication will be based on the most recent version of the British National Formulary Royal Pharmaceutical Society of Great Britain.^54^

Individual-level responses on the EQ-5D-Y will be used to estimate health-related quality of life based on a UK population valuation set. Subsequently, an area under the curve approach will be used to calculate QALYs for each child. QALY is a utility-based measure, that is, it measures each person’s health state in terms of quality of life dimensions and then weights it on the value or utility of the health state based on UK population preferences.^55^

The primary economic analysis will be cost–utility analysis conducted over the trial follow-up period (6 months). Total costs, including the intervention cost and service utilisation costs, and QALYs, will be compared between the two interventions. Unadjusted costs and outcomes will be presented in a descriptive analysis using parametric and non-parametric tests. The statistical analysis will compare mean costs and QALYs using a regression model. The regression analysis will control for baseline differences in utility.^56^ The specification of the model will follow the approach recommended by Glick *et al*
57 which considers the distribution of the dependent variable as well as any correlation between the cost and QALY outcomes. The regression coefficient on treatment will then represent the difference in mean cost and mean QALYs between groups. A bootstrap method will be used to produce CIs around the cost and QALY differences due to the likely skewness in the distribution of regression residuals.^58^ To present this in the UK decision-making context, the results will be in the conventional form of a cost-effectiveness acceptability curve (CEAC). CEAC presents the probability of the intervention being cost-effective over a range of willingness-to-pay (WTP) thresholds per QALY.^59^ The higher the probability, the more likely it is that the treatment is cost-effective at the particular WTP threshold.

The following sensitivity analyses will be conducted; (1) a cost–utility analysis using the CHU-9D instrument instead of EQ-5D; (2) a cost-effectiveness analysis using a phobia-specific measure instead of a utility-based measure and (3) cost–utility analysis from a health services perspective.

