#### Resource Utilisation Questionnaire

We developed a bespoke questionnaire to assess use of healthcare and other resources, based on a previous Resource Utilisation Questionnaire by Barrett and colleagues^45^ and its adaptations for younger populations by members of our research team^45–47^ The questionnaire is completed by the parent and collects data on resource and service utilisation relating to the child over the previous 6 months on: general health and community service use (ie, appointments with GP’s, nurses, social services and educational services); mental health service use (ie, appointments with a psychiatrist, psychotherapists, psychologists, CAMHS therapists and other forms of mental health support); hospital-based services (ie, visits to A&E, urgent care centres and hospital stays); days missed from school by the child; days missed by parents/carers from work or studies.

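### The economic regression names baseline utility as its one covariate and no therapist clustering, although the clinical model uses site, age group, severity and therapist, and baseline resource use is collected

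*Protocol article*

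**What the plan says.** Under Economic evaluation, mean costs and QALYs are compared by regression. The article states that "The regression analysis will control for baseline differences in utility". The rest of the specification follows a cited approach "which considers the distribution of the dependent variable as well as any correlation between the cost and QALY outcomes". For uncertainty, "A bootstrap method will be used to produce CIs around the cost and QALY differences", and the reason given is the likely skewness of the residuals. The results then feed a cost-effectiveness acceptability curve. The section does not mention therapist, site, age group, severity or baseline cost, and it does not give the bootstrap's resampling unit.

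Under Data analysis, the primary and secondary outcomes, with EQ-5D-Y and CHU-9D among the secondary ones, are compared by "mixed-effects linear regression with exchangeable correlation to allow for the clustering of outcomes within therapist", "controlling for baseline BAT score, site and stratifying variables (age group and baseline phobia severity").

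Under Sample size, treatment is delivered by "therapists who will see approximately 15 patients each", with an assumed ICC of 0.01 and a design effect of 1.14.

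The Resource Utilisation Questionnaire "collects data on resource and service utilisation relating to the child over the previous 6 months". It is among the measures that Outcome measures schedules at baseline and at 6 months.

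**The concern.** The same children's EQ-5D-Y responses are handled in two ways. As a clinical secondary outcome they get a model with site, the stratifying variables and therapist. Turned into QALYs, they get a model described with one covariate and no cluster term. The article gives no reason for the difference. A therapist effect judged real enough to raise the sample size by 14% does not vanish when the score becomes a QALY.

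For cost, therapist or site effects are at least plausible. The article says that CBT can run from 4 to 20 sessions, that practitioners come from several professions and sectors, and that care pathways differ between sites. A bootstrap that resampled individual children would deal with skewness but not with dependence within therapist.

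Baseline utility is the natural covariate for QALYs, and baseline cost is its counterpart for costs. The data for it are already planned. Value for money is one of the three stated aims, so the intervals and the acceptability curve carry weight.

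**Working it through.** **Inputs from the protocol article (Sample size):** margin 0.4 SD; baseline-final correlation 0.5; one-sided alpha 2.5%; power 90%; 15 children per therapist; ICC 0.01 (set for the BAT); 20% drop-out. The economic section gives no figure of its own.

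**1. The plan's own figure.** With residual SD √(1 − 0.5²) = 0.866, n per arm = 2 × (1.960 + 1.282)² × 0.75 / 0.4² ≈ 98.5, so 99 (stated: 100). Design effect = 1 + (15 − 1) × 0.01 = 1.14; 100 × 1.14 = 114; 114 / 0.8 = 142.5, so 143 per arm and 286 in total. The sample size reproduces, and with it the size of the therapist effect that the plan assumes.

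**2. If therapist clustering is left out of the economic intervals.** With DE = 1 + 14 × ICC, the unclustered SE is too small by 1 − 1/√DE. Coverage of a nominal 95% CI is 2Φ(1.96/√DE) − 1. An acceptability probability p becomes Φ(z_p/√DE).

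| ICC | DE | SE too small by | Coverage | 0.90 becomes |
|---|---|---|---|---|
| 0.01 (plan) | 1.14 | 6.3% | 93.4% | 0.885 |
| 0.02 (assumed) | 1.28 | 11.6% | 91.7% | 0.871 |
| 0.05 (assumed) | 1.70 | 23.3% | 86.7% | 0.837 |
| 0.10 (assumed) | 2.40 | 35.5% | 79.4% | 0.796 |

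Only the first row uses the plan's ICC, and that ICC was chosen for the BAT, not for cost or QALYs. All rows take therapists as nested within arm, as the plan's design effect does.

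**3. If clustering arises in the CBT arm alone.** OST has a fixed format, so clustering driven by the number of sessions would sit in the CBT arm. With equal cost variances (an assumption), the design effect for the contrast is the mean of the two arms: (1 + 1.70)/2 = 1.35 and (1 + 2.40)/2 = 1.70. Coverage is then about 91% and 87%, instead of 86.7% and 79.4%.

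**4. If baseline cost is left out.** Adding a covariate with correlation r to follow-up cost multiplies the SE by √(1 − r²). For r = 0.3 this is 0.954 (about 5% narrower), and for r = 0.5 it is 0.866 (about 13% narrower). Both values of r are assumptions.

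**5. Number of therapists.** 143 / 15 ≈ 9.5, so roughly 10 per arm.

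**The case against.** A reader might infer that the economic regressions adjust for nothing but baseline utility, that the bootstrap resamples individual children, and that the CIs and acceptability curve are therefore too certain. The document does not support that. It names one covariate but does not exclude others. It defers the specification to a cited approach that cannot be seen here, and it does not state the resampling unit. A condensed article may leave such detail to a fuller protocol or a health economics analysis plan. This stands: no error in the economic intervals has been shown.

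Nor is a net direction established. Omitted clustering makes intervals too narrow. Omitted baseline cost or stratifying variables makes them wider than they need be, and under randomisation does not bias the cost difference. The two effects should not be added into one headline.

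The size is also open to challenge. Coverage of 79% to 87% needs assumed ICCs of 0.05 to 0.10, for which the article gives no basis. Total cost also includes service use and absenteeism, which an argument from session numbers does not reach. No section says that each therapist delivers only one treatment; if therapists treat both arms, their effects partly cancel from the contrast and the understatement shrinks or may vanish. With about 10 therapists per arm, a therapist-level bootstrap or multilevel model is itself somewhat unstable. All of this stands, and it limits the size of the point and the strength of the remedy.

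It does not remove the mismatch. The article describes the economic model in some detail (a covariate, the outcome distribution, the cost-QALY correlation, the reason for the bootstrap), and nothing in that description carries over the clustering and design variables used a few paragraphs earlier for the same children.

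**Conclusion.** The point holds as a modest, concrete improvement to the model as described. It is not a demonstrated error. On the plan's own figures, omitting therapist clustering would understate economic standard errors by about 6%, which is unlikely on its own to change a decision. The error is larger only if the ICC for cost or QALYs is well above 0.01, and smaller if therapists treat both arms. Separately, leaving out baseline cost would give up about 5% to 13% of the width of the cost CI at assumed correlations of 0.3 to 0.5, which is lost precision and not false certainty. The case for changing the text is that the change is nearly free, the data are already collected, and the economic analysis would then match the plan's own assumptions about therapists and design variables.

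**What to change.** State the two equations in the economic analysis plan:

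- **QALYs:** treatment, baseline utility, age group, severity and site.
- **Costs:** treatment, baseline 6-month cost from the Resource Utilisation Questionnaire, age group, severity and site.
- **Uncertainty:** account for therapist in the CIs and the acceptability curve, for example by a bootstrap that resamples therapists and then children, or by a multilevel bivariate model. With roughly 10 therapists per arm, doing this at least as a sensitivity analysis is reasonable. State the resampling unit of the main bootstrap, and whether therapists deliver one treatment or both.

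If the economic model is meant to differ from the clinical one, say so and give the reason.

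The cost is some plan text and slightly more code, with no new data. Intervals may widen slightly once clustering is counted, and cluster methods are less stable with so few therapists.
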